#### Body composition

A whole-body dual-energy x-ray absorptiometry (DXA) scan will be used to measure lean mass (in grams) and other components of body composition (e.g., fat mass, body fat percentage, appendicular lean mass, fat free mass, visceral fat, etc.). The APEX version 4.0 software within the Hologic Discovery A QDR series DXA system (Waltham, MA) will be used following standard procedures for testing and quality control calibration prior to testing [45, 46].

#### Fatigue

The Functional Assessment of Chronic Illness Therapy-Fatigue (FACIT-Fatigue) version 4 will be used to evaluated fatigue via a score assigned upon completion of the questionnaire. FACIT-Fatigue questionnaire consists of 13 items and includes a reliability coefficient of about 0.90 [47].

#### Physical function

Both objective and subjective measures will be used to evaluate changes in physical function throughout the duration of the 52-week trial. The short physical performance battery will be used as an objective measure to evaluate physical function [48, 49], and will be carried out within the physical assessment portion of the POWER program assessment. The short physical performance battery used for this trial consists of the following three tests: 4-meter walk test, standing balance, and 5-time chair stand test. Participants will receive a score for each test within the battery and a total score for all three tests. Additionally, the PROMIS physical function short form 6b will be used as a subjective measure of physical function. This questionnaire includes six items, and an average reliability coefficient is 0.95 [50].

#### Whole-body strength

Handgrip strength will be evaluated as a measure of whole-body strength, in kg, with use of a portable, hydraulic dynamometer (Jamar 5030J1). Participants will be instructed to sit upright in a chair, keeping feet flat on the floor, shoulders square, and elbow flexed in a 90-degree angle with their forearm of the testing hand resting on a Table [51]. They will then be instructed to squeeze the instrument as hard as they can for 5 s, repeating two more times with a 2-minute rest between sets. This test will be done on each hand, and the best measurement of the three repetitions on each side will be recorded in the study database.

#### Independence

The Katz Index of Independence in Activities of Daily Living (ADL) questionnaire will be used to assesses independence to complete ADLs via a score. The survey has an interrater reliability coefficient of 0.95 [52]. This is a 6-item questionnaire that covers six domains of independence (bathing, dressing, toileting, transferring, continence, and feeding) and is widely used by clinicians to assess ability to perform ADLs [53].

#### Quality of life

The Functional Assessment of Cancer Therapy- Prostate (FACT-P) version 4 includes prostate cancer-specific questions within the assessment of quality of life, via a score. The questionnaire includes 39 items among the following domains: physical well-being, social/family well-being, emotional well-being, functional well-being, and additional concerns. The reliability coefficient of FACT-P is 0.87–0.89 [54].

#### Insulin sensitivity

Fasting serum glucose and insulin will be measured and the homeostatic model of assessment for insulin resistance (HOMA-IR) will be calculated for each time point [55]. The timing of the participant’s study assessments will align as closely as possible with standard of care (SOC) clinic visits. Blood drawn for research purposes will occur in tandem with clinical orders. In the event the participant’s study period is not closely aligned (e.g., at least 2 weeks) with SOC visits, an additional blood draw will need to occur and will be carried out by the hospital’s diagnostic laboratory. Blood collected for insulin sensitivity evaluation will be transferred immediately to Associated Regional University Pathologists (ARUP) laboratory (Salt Lake City, UT) for processing to serum and analysis. ARUP laboratory is the diagnostic laboratory associated with the University of Utah hospital system and is located adjacent to the University of Utah academic and medical campus. Results for glucose and insulin will be extracted from the medical record by the study team.

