#### Participant population

Participants will be recruited from the genitourinary medical oncology clinics at HCI at the University of Utah in Salt Lake City, Utah. The study team’s clinical research coordinators, [name], will be responsible for obtaining informed consent, carrying out screening procedures, and enrolling participants. Table 1 lists key eligibility criteria. Please see ClinicalTrials.gov registration for a complete list of eligibility criteria (NCT06112990).

**Table 1 Tab1:** Key Eligibility Criteria

Inclusion Criteria
1. Subject age ≥ 18 years old
2. Metastatic castration-sensitive prostate cancer patients who have not met standard criteria for disease progression on current systemic therapy
3. Currently treated with surgical castration or medical castration with GnRH agonists/antagonists, and/or an androgen receptor pathway inhibitor (e.g., abiraterone, enzalutamide, apalutamide, darolutamide) ^*^
4. ECOG Performance Status ≤ 2
5. Not currently adhering to national physical activity guidelines for resistance training, as defined as participating in structured resistance training ≥ two days per week.
6. Regular access to an electronic device with internet service and ability for video calls
7. Access to an active MyChart account or the willingness to create an account for the purposes of the trial
8. Willingness to engage in a home-based resistance exercise program two days per week
9. Willingness to take creatine monohydrate supplementation or placebo for the duration of the 52-week trial and to avoid taking additional creatine-containing supplementation or other nutritional supplementation during the study period
10. Willingness to complete and submit weekly supplementation logs to study personnel throughout the duration of the 52-week study via email, text, in person, or verbally verified over the phone
11. Willingness to complete three in-person assessment sessions (baseline, 24-, and 52-weeks)
12. Able to provide informed consent and willing to sign an approved consent form that conforms to federal and institutional guidelines
Exclusion Criteria
1. Treatment with cytotoxic chemotherapy within 12 weeks prior to enrollment
2. eGFR < 30 ml/min/1.73m^2^

GnRH- Gonadotropin hormone-releasing hormone

* Must have started the current regimen at least 12 weeks prior to enrollment

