Participants will receive supplementation (creatine or placebo) at baseline and 24-week assessments and retrieve their supplementation at the HCI IDS Pharmacy. Upon retrieval, a pharmacist will verbally review directions for supplement administration with the participant along with providing an information sheet that recapitulates the directions verbally provided. Regardless of group the participant is randomized to, directions for supplementation use are the same, and based on a well-established protocol [30]. Week 1 is considered the loading phase. Here participants will be instructed to consume five grams of supplementation four times daily, with each dose consumed with 16 fluid ounces of a carbohydrate-containing beverage. The loading phase is established with demonstrated safety in apparently healthy and clinical populations [30, 38, 43, 44], including data from our group which demonstrates safety among men living with mCSPC on ADT (NCT03987217). Weeks 2–52 is considered the maintenance phase. Here participants will be instructed to consume five grams once per day with 16 fluid ounces of a carbohydrate-containing beverage. Creatine monohydrate supplementation contains zero calories per five gram serving. The placebo, which is dextrose, contains 20 calories per five gram serving. For participants who are insulin resistant, a member of the study team will help strategize ways to fit the supplement in his diet. This dietary guidance will be supervised by [name], who is a Registered Dietitian with clinical experience in diabetes care.

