### Assessment procedures & study outcomes

Participants will be instructed to refrain from strenuous exercise at least 24 h before each scheduled assessment session, fast for at least eight hours prior to the blood draw associated with each session, and follow their usual diet and medication regimen. Table 2 outlines study outcomes and procedures.

**Table 2 Tab2:** Study outcomes and assessment procedures

Outcome	Procedure
Muscle Mass*	Whole-body DXA Scan
Fatigue	FACIT-Fatigue Questionnaire
Physical Function	PROMIS Physical Function Questionnaire
	Short Physical Performance Battery
Strength	Handgrip Strength Test
Independence	Katz Index of Independence in Activities of Daily Living
Insulin Sensitivity (HOMA-IR)	Calculated from measured fasting insulin & glucose**
Fat Mass	Whole-body DXA scan
Serum PSA	Blood Draw
cell-free DNA	

*Primary outcome; **Fasting insulin and glucose assessment requires a blood draw

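### HOMA-IR is calculated at each visit with usual medication continued and no stated exception for exogenous insulin: a cheap improvement for one secondary outcome

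*Protocol article*

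**What the plan says.** The Insulin sensitivity section says that "the homeostatic model of assessment for insulin resistance (HOMA-IR) will be calculated for each time point". Table 2 gives the source as "Calculated from measured fasting insulin & glucose". Neither place names a marker of the patient's own insulin production or an exception for men who inject insulin.

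Participants are told to "follow their usual diet and medication regimen" around assessments, and the Research design section gives the same instruction for the trial as a whole.

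The two exclusions shown in Table 1 are "Treatment with cytotoxic chemotherapy within 12 weeks prior to enrollment" and "eGFR < 30 ml/min/1.73m^2". Neither these nor the inclusion criteria shown mention diabetes or insulin. The table lists key criteria only: "Please see ClinicalTrials.gov registration for a complete list of eligibility criteria".

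The supplementation section foresees men with impaired glucose metabolism: "For participants who are insulin resistant, a member of the study team will help strategize ways to fit the supplement in his diet". The supervisor of that advice is described as someone "who is a Registered Dietitian with clinical experience in diabetes care".

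Under Statistical analysis, secondary endpoints follow the muscle-mass approach: a mixed model in all randomized participants with baseline assessments, adjusted for age, time on ADT and ECOG status. Changes in insulin sensitivity are also related to changes in cfDNA and PSA, overall and within each arm.

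**The concern.** HOMA-IR is proportional to the product of fasting insulin and fasting glucose, and it reads the insulin as the patient's own output. In a man on injected insulin, the measured concentration may reflect his dose and the time since injection. The index then no longer describes his sensitivity.

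Taken together, the stated rules would put such values into the analysis: calculation at each visit, medication continued, all modified intention-to-treat participants included. At stake is the precision and the meaning of one named secondary outcome, and of the exploratory models that use its change. With roughly 100 men per arm, a few extreme values can carry weight, especially in the within-arm models.

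**Working it through.** **Reading the text.** The plan states no HOMA-IR figure, so there is nothing to reproduce. The check sets the rules side by side.

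1. *Could insulin users be present?* No key criterion shown excludes them. The full list is elsewhere, so their enrolment is possible but not established. The article also says that ADT leads to declines in insulin sensitivity, so glucose-lowering treatment could be started during 52 weeks.
2. *Would their values be calculated?* The calculation rule has no stated exception, and usual medication continues.
3. *Would the values be analysed?* Secondary endpoints mirror the primary model. Insulin use is not a covariate, an exclusion or a stratification factor (the factors are age and ECOG status).
4. *Does the article set validity rules elsewhere?* Yes: cfDNA samples yielding under 5 ng are treated as inadequate for analysis. HOMA-IR has no comparable rule.

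**Illustration 1 (log scale, simulated).** All inputs are assumptions except the 100 per arm: true difference in log HOMA-IR change 0.25, SD of change 0.5, two-sided 5% test. A share q of each arm uses insulin. In these men there is no treatment effect, and extra noise of SD 0.5 or 1.0 is added, giving an SD of √(0.5² + extra²). There were 20,000 runs per scenario. The expected estimate is (1 − q) × 0.25.

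| Share q | (1 − q) × 0.25 | Simulated mean | Power, extra SD 0.5 | Power, extra SD 1.0 |
|---|---|---|---|---|
| 0% | 0.250 | 0.250 | 94.5% | 94.3% |
| 2% | 0.245 | 0.245 | 92.7% | 91.4% |
| 5% | 0.2375 | 0.238 | 90.3% | 86.0% |
| 10% | 0.225 | 0.225–0.226 | 85.7% | 76.2% |

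The 0% row differs between columns only by simulation error. With no true effect, the mean difference was about 0 and the rejection rate 4.9% to 5.3% throughout.

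**Illustration 2 (raw scale, by formula).** Again all assumed: SD of change 1.5 in non-users and s = 5 to 8 in users, equal means, difference 0.65, 90 per arm. This shows noise only, without dilution.

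Overall SD = √((1 − p) × 1.5² + p × s²); power = Φ(0.65 / (SD × √(2/90)) − 1.96).

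- p = 0: SD 1.5; 0.65/0.2236 − 1.96 = 0.95; power 83%.
- p = 3%, s = 5: SD = √(2.1825 + 0.75) = 1.71; power 72%.
- p = 3%, s = 8: SD = √(2.1825 + 1.92) = 2.03; power 58%.
- p = 8%, s = 5: SD = √(2.07 + 2.00) = 2.02; power 58%.
- p = 8%, s = 8: SD = √(2.07 + 5.12) = 2.68; power 37%.

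The two illustrations agree in direction and differ widely in size. The article fixes neither the scale of analysis nor any of the inputs.

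**The case against.** The strongest reply is that this rests on things not shown. Table 1 is a selection, and the registry list may exclude insulin-treated men. A full protocol or SAP may already say which HOMA-IR values are evaluable, and an article often leaves that to them. Defining HOMA-IR from fasting glucose and insulin is not wrong in itself and contradicts nothing else in the text. This stands, and it keeps the point at low severity.

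A reader might infer from the supplementation section that insulin-treated men are expected. The text does not say so. Insulin resistant is not the same as insulin treated. The sentence follows the statement that the dextrose placebo has 20 calories per serving, and the supervisor's diabetes-care experience is a credential, not an eligibility statement.

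A reader might also infer that the comparison is biased. With blinded 1:1 allocation, a chance uneven split of insulin users is ordinary sampling error, and the simulation shows no inflation of type I error. A systematic difference would need insulin to be started or changed differently by arm. With a dextrose placebo that is conceivable, but nothing in the documents shows it.

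Nor does the injected-drug argument extend to other glucose-lowering drugs, which do not enter the insulin assay as injected insulin may.

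Finally, dropping every visit with insulin use would have a cost. Starting insulin after randomization may itself reflect worsening of the outcome under study, so such a rule would condition on a possible effect of treatment. That objection is sound, and it shapes the fix.

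**Conclusion.** The point holds conditionally. As written, the rules would produce and analyse HOMA-IR values that do not measure insulin sensitivity in any man using exogenous insulin. Whether there will be such men cannot be told from the article, so the stronger statement that the comparison is contaminated is not supported.

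If they are present, expect noise and attenuation in one secondary outcome and in the exploratory models that use it, without an expected spurious arm difference. The size cannot be derived from the documents. The power losses shown rest wholly on assumed shares, SDs and effects, and the 37% figure comes from the most extreme pairing. The primary muscle-mass analysis is unaffected. This is a cheap improvement of low severity.

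**What to change.** Leave eligibility and treatment unchanged, and add the following to the Insulin sensitivity section or the SAP, before unblinding:

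- Define the HOMA-IR analysis set as participants not using exogenous insulin at baseline. This conditions only on a fact fixed before randomization, so the randomized comparison is kept. Report fasting glucose for all participants.
- Record glucose-lowering drugs at baseline, 24 and 52 weeks from the medical record, which the team already uses for laboratory results.
- Report by arm how many participants start insulin after baseline. Keep their values in the main HOMA-IR analysis, and add a sensitivity analysis that sets aside HOMA-IR at visits after insulin is started, labelled as conditioning on a post-randomization event.

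The cost is a few sentences and one item of data extraction. The downside is that a few participants may not contribute to this one secondary outcome. If the full criteria already exclude insulin users at entry, the first step removes nobody, and the other two still cover insulin started during follow-up.

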#### Markers of cancer progression

Serum Prostate Specific Antigen (PSA) and cell-free DNA (cfDNA) will be measured to evaluate changes in markers of cancer progression. Serum PSA, in ng/mL, is measured as standard of care. Collected blood will be transferred to ARUP for analysis and data will be extracted from the medical record by the study team. Blood for cfDNA analysis will be collected in K2-ethylenediamine tetra-acetic acid anticoagulant collection tubes along with other study blood as described above. After collection, these samples will be transferred to HCI’s Biorepository and Molecular Pathology for processing. These samples will be centrifuged at 2,000 g for 10 min, with a brake speed of 7. Plasma will be aliquoted to cryovials and centrifuged once more at 1,500 g for 5 min. Samples will then be stored at -80^◦^C until batch analysis upon completion of data collection.

Upon completion of data collection, circulating cfDNA will be extracted using Maxwell® RSC 48 as per manufacturer’s specifications and using pre-designated kits per manufacturer, which include the Maxwell® CSC Whole Blood DNA Kit for genomic DNA and the Maxwell® RSC for circulating cfDNA. Extracted circulating cfDNA will then undergo quantity and quality check using Qubit 3.0 Fluorometer (Thermo Fisher Scientific, Waltham, MA, USA) and Bioanalyzer 2100 (Agilent Technologies, Santa Clara, CA, USA). For samples with severe genomic contamination from peripheral blood cells, a size selection will be performed with AMPure XP beads (Beckman Coulter, Brea, CA, USA) to remove large genomic fragments. Samples with a total yield < 5 ng will be considered inadequate for formal analysis or for downstream next generation sequencing methods.

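### The blood-draw alignment rule does not require baseline insulin, glucose and cfDNA samples to precede the first supplement dose

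*Protocol article*

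**What the plan says.** All references are to the protocol article.

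- **Insulin sensitivity.** The stated aim is that "study assessments will align as closely as possible with standard of care (SOC) clinic visits". The default source of the sample follows: "Blood drawn for research purposes will occur in tandem with clinical orders". The exception is a study period that is "not closely aligned (e.g., at least 2 weeks) with SOC visits, an additional blood draw will need to occur". The rule is written for all time points together.
- **Creatine monohydrate & placebo supplementation.** "Participants will receive supplementation (creatine or placebo) at baseline and 24-week assessments". "Week 1 is considered the loading phase", and the instruction for that week is "five grams of supplementation four times daily, with each dose consumed with 16 fluid ounces of a carbohydrate-containing beverage". The first-dose date is not tied to the blood draw.
- **Assessment procedures & study outcomes.** Participants are told to "fast for at least eight hours prior to the blood draw associated with each session".
- **Research design.** Plasma for cfDNA is listed among the baseline, 24-week and 52-week procedures. PSA results are routine-care values taken from the patient record at those times.
- **Markers of cancer progression.** cfDNA blood is collected "along with other study blood as described above", so it follows the same timing rule as insulin and glucose.
- **Statistical analysis.** Secondary endpoints are analysed like muscle mass, by comparing baseline-to-follow-up change between arms. Further models relate changes in cfDNA and PSA to changes in other outcomes, with the baseline value of the endpoint as a covariate.

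**The concern.** A baseline value has to be free of treatment. Randomisation makes the arms comparable in expectation only for what is measured before exposure begins. The alignment rule is a sensible convenience at weeks 24 and 52, where a visit may fall a few days either side of the target. At baseline the two sides differ: a draw before the assessment is still pre-exposure, while a draw after it may fall in or beyond the loading week.

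What is at stake is the reference value for HOMA-IR and cfDNA. If it is taken after dosing, it is a post-randomisation measurement, and any arm difference that has already developed is removed from the estimated change. The models that adjust for the baseline endpoint value would then adjust for something treatment may have altered. The models that relate cfDNA change to body-composition change could pair a pre-dose DXA scan with a post-dose blood sample in the same participant.

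**Working it through.** The plan gives no figure on this point, so there is none to reproduce. The check is a reading of the timing statements together, followed by the algebra of the consequence.

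**1. Timing.** Call the day of the baseline assessment day 0 and the clinic visit day *d*. The extra draw is triggered at a mismatch of about 2 weeks or more, so by that example any visit with |*d*| < 14 supplies the research blood. Supplement is in the participant's hands from day 0. If dosing starts on or soon after collection (an assumption, since the first-dose day is not stated):

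| Clinic visit | Separate draw triggered? | Sample relative to dosing |
|---|---|---|
| day −13 to −1 | No | Before exposure |
| day 0 (same day) | No | Before exposure if drawn before the first dose; the order is not stated |
| day +1 to about +7 | No | During loading |
| about day +8 to +13 | No | After loading, in maintenance |
| 14 days or more either way | Yes | Depends on when the extra draw is made |

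The third and fourth rows satisfy the rule as written.

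**2. Do the other sections close the gap?** Listing plasma collection at baseline, and attaching a fasting draw to each session, both point to a same-session sample. But the alignment rule exists for the case where session and clinic visit do not coincide, and it accepts the clinic draw when the mismatch is under about 2 weeks. Neither of the other statements adds a pre-dose condition.

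**3. Exposure by arm in the loading week.** Placebo dextrose carries 20 calories per 5 g serving and creatine none. Four servings a day give 4 × 20 = 80 calories a day of dextrose against 4 × 0 = 0. The drink taken with each dose is the same in both arms.

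**4. Effect on the estimate.** Let Δ be the true arm difference in the marker at follow-up. With every baseline drawn before dosing, the expected arm difference at baseline is 0 and the difference in change is Δ − 0 = Δ. If a share *p* of baselines in each arm is drawn after dosing, and a fraction *f* of Δ is present by then, the expected baseline difference is *p* × *f* × Δ. The difference in change becomes Δ − *pf*Δ = Δ(1 − *pf*).

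Illustration only; *p* and *f* are assumed, not taken from the documents:

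| *p* | *f* | Loss, *p* × *f* |
|---|---|---|
| 0.10 | 0.10 | 1% |
| 0.25 | 0.25 | 6.25% |
| 0.50 | 0.50 | 25% |

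If no baseline is drawn late (*p* = 0) or nothing has changed by then (*f* = 0), the loss is zero. If an early effect ran opposite to the later one (*f* < 0), the estimate would be inflated instead.

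**The case against.** The strongest reply is that the gap is inferred from silence. The text schedules assessments to fall with clinic visits, lists plasma collection at baseline and ties a fasting draw to each session, so the intended practice is evidently one visit with everything done together. The 2-week figure is given only as an example. This is a condensed article, and the order of baseline procedures relative to the first dose may well be set in the full protocol or a laboratory manual.

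Much of that stands. The article does not plan a post-dose baseline, and a reader who inferred that it does would go too far. What remains is that the article does not leave timing open: it states a rule, and that rule, applied as worded, admits a late baseline sample. The intention elsewhere is not put as a condition that would override it.

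It is also fair that nothing in the article shows that a week of loading moves these markers. Samples are fasting, and the carbohydrate drink is common to both arms. A reader might infer that loading raises baseline insulin in both arms and makes later values look like improvement; the documents give no support for that.

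**Conclusion.** The point holds as a defect in a stated timing rule: nothing in the article excludes a baseline fasting insulin, glucose or cfDNA sample taken after the first dose. This rests on two readings: that the 2-week tolerance applies at baseline as at other visits, and that dosing may begin before a clinic visit falling within that tolerance.

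The size of any bias is unknown. The 1% to 25% range follows from assumed inputs and is not an estimate for this trial. The consequence is confined to secondary endpoints; the primary DXA measure of muscle mass is unaffected.

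Three wider readings are not supported:

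- **PSA.** A reader might place PSA under the same rule. That rule governs research blood, whereas PSA is a routine-care value taken from the record. Its baseline window is simply not stated, which is a smaller matter that can be settled in the same edit.
- **Frequency.** A reader might suppose that about half of off-day baseline draws fall after dosing. That would need clinic visits spread evenly around the assessment, which the article does not say, and it aims for the closest possible alignment.
- **Week 52.** A reader might extend the concern to a draw after supplementation ends. That is ordinary follow-up tolerance rather than a compromised reference value, and the documents show no resulting distortion.

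**What to change.** Add one sentence to Insulin sensitivity: blood for baseline insulin, glucose and cfDNA must be drawn before the first supplement dose, so that the alignment window at baseline runs backwards only; if no clinic draw meets this, the additional draw already provided for is used. Cross-refer to it from Markers of cancer progression, and state there that baseline PSA is the latest routine-care value before the first dose. Weeks 24 and 52 can keep the existing tolerance.

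The cost is a few more stand-alone baseline draws, of a kind the plan already allows. The article describes the trial as open to enrolment, and a sample taken too late cannot be made pre-exposure by analysis, so the edit is worth making promptly. For participants already enrolled, comparing the draw date with the first entry in the daily supplementation log would show whether any baseline is affected.
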